#### Data collection

Prior to randomisation, the research team will collect baseline demographic and clinical characteristic data from the electronic medical record. Data include general demographics, reason for intubation, date of hospital and ICU admission, date of intubation, admission Acute Physiology and Chronic Health Evaluation (APACHE II), baseline ventilator settings, and airway type and size (Table 1).

Clinical outcomes (Table 1) will be measured before, on completion, and 5 min after physiotherapy sessions for both study arms. We have selected exploratory clinical outcomes using the core outcome measure set for critical care ventilation trials [20]. In addition, we will record the number and type of physiotherapy treatments provided, patient pain/discomfort, cardiovascular parameters, ventilatory parameters, and respiratory parameters (see Table 1 for further details).

To assess the feasibility of collecting data for a cost-utility analysis in a future trial, we will collect the following:EQ-5D-5L at 6-month post-ICU dischargeResource use associated with the MI-E intervention and standard care

We will identify the following resource use during the index admission: MI-E device-associated resource use including staffing requirements (time spent delivering an MI-E treatment, grade/seniority of staff administering treatment) and consumables used. Patient-related resource use will include endotracheal suction frequency by nursing staff (over a 24-h period), use of noninvasive ventilation (NIV), high-flow oxygen therapy (HFOT) and tracheostomy, antibiotic use, physiotherapy on-call use (planned and unplanned), ICU LOS, ICU re-admission and hospital LOS. For the purposes of the feasibility trial, these will be reported as frequencies and time duration (hours).

### Clinician training

Training for physiotherapists detailing the study protocol and how to deliver the intervention will occur at the start of the study. Standardised education materials developed by the research team will be distributed to all clinicians with the opportunity to practice intervention set up and delivery.

### Outcome description

*Re-intubation rate*: Re-intubation rate will be calculated for the 48 h following extubation. This is the planned primary outcome for the future planned trial.*Pain scores*: We will measure pain using the ‘numeric rating scale’ (NRS) [21] and the Critical Care Pain Observation Tool (CPOT) [22]. All patients will have CPOT measured. The CPOT is a valid measure to determine pain presence with four domains: facial expressions, body movements, compliance with the ventilator or vocalisation, and muscle tension. Each domain is scored 0–2 with a maximum score of eight. A CPOT score > 2 indicates pain presence. The NRS is a self-reported measure where patients rate pain presence and severity on a scale from 0 (no pain) to 10 (worst pain possible). During PPI work, patients highlighted the importance of including a patient-reported outcome. The NRS will be measured in addition to the CPOT. If a patient is unable to rate pain, we will use the CPOT only. We will document pain presence before and after a physiotherapy session.*Cardiovascular, ventilator, and respiratory parameters*: These measures include heart rate, systolic and diastolic blood pressure, ventilator settings, airway resistance and lung compliance, peripheral oxygen saturations, and respiratory rate measured pre- and post physiotherapy in both the intervention and control arms.*Acceptability*: We will use three validated questionnaires to measure acceptability: acceptability of intervention measure (AIM), intervention appropriateness measure (IAM) and feasibility of intervention measure (FIM) [23]. These will be measured immediately post-MI-E intervention.

#### Statistics and data analysis

##### Sample size calculation

As this is a feasibility trial, a formal sample size calculation based on statistical power to detect a specified treatment effect size is not appropriate. We have selected a sample size of 50 participants based on measurement of feasibility parameters with adequate precision. The participating ICU admits approximately 1250 patients annually with potentially four to five eligible patients each week (minimum of 200 per year). We anticipate recruiting 50 over a 12-month period would be achievable, with an estimated recruitment rate of 25% and a confidence interval width of 0.12.

##### Statistical analysis plan

The analysis and reporting of this study will be consistent with the CONSORT guidelines extension to feasibility studies [24]. This study is not designed or powered to carry out formal hypothesis testing. Participant flow through the study will be summarised and presented in a flow diagram. Descriptive statistics for patient characteristics will be reported overall and by treatment group: as means or medians with measures of dispersion for continuous outcomes (as appropriate given distribution) and frequencies and percentages for categorical outcomes. Only descriptive statistics will be used in the physiology sub-study due to the small sample size proposed. Patient-reported and clinical feasibility outcomes will be presented and assessed for completeness of data.

##### Safety reporting

The attending consultant physician is responsible for assessing all adverse reactions and adverse events (AEs) and categorising seriousness, expectedness, and relatedness. A list of events that can be expected during this trial, or within this patient population, can be found below.Accidental extubation during the interventionCardiovascular changes (including but not exclusive to hypo/hypertension, brady/tachycardia, arrhythmias)PneumothoraxSputum plugging during the interventionPulmonary complications such as pneumoniaMinor skin irritations due to electrical impedance tomography electrode patch application.

We will record occurrence of the following during a MI-E treatment and control arm interventions: HR, SBP, and DBP increase/decrease > 20% baseline and requiring intervention, arrhythmia (requiring intervention), pneumothorax, acute desaturation to < 85% or > 10% below baseline and requiring intervention, accidental extubation, and cardiopulmonary arrest.

It is the responsibility of the sponsor, chief investigator, and delegated individuals to ensure that the dignity, rights, safety, and well-being of research participants are given priority at all times, and appropriate action is taken to ensure their safety. The recording and reporting of safety events will be in accordance with good clinical practice (GCP) guidelines and study sponsor’s ‘research safety reporting’ standard operating procedure.

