**Fig. 1 Fig1:**
[figure not shown]
Study flow chart

**Table 1 Tab1:** Schedule for enrolment, intervention, and follow-up

	**Data**	**Timepoint**						
		**Enrollment**	**Baseline**	**Pre-intervention**	**During intervention**	**5 min post intervention**	**Duration of study period**	**6-month follow-up**
**Enrolment**	Eligibility screening	X						
	Consent	X						
	Allocation	X						
**Intervention**	Standard care				X			
	MI-E intervention				X			
**Assessments: baseline demographic outcome**	Demographics (age, gender, predicted body weight, history of lung disease, smoking history)		X					
	Reason for intubation		X					
	Date of hospital and ICU admission		X					
	Date of intubation		X					
	Ventilator settings		X					
	Airway type and size		X					
	APACHE II score		X					
**Assessments: clinical outcomes**	Use of HFOT, NIV, tracheostomy						X	
	Use of physiotherapy interventions				X			
	LUS score			X		X		
	Patient pain/discomfort (CPOT; NRS)			X		X		
	CVS parameters (HR, SBP, DBP)			X		X		
	Ventilator parameters (vent settings, resistance, compliance)			X		X		
	Respiratory parameters (RR, SpO_2_)			X		X		
**Assessments: health economics**	• Resource use (staffing requirements, suction frequency, consumable use, antibiotic use, physiotherapy on-call use) • QoL (EQ-5D-5L)				X			X
**Assessments: safety**	Adverse events				X	X	X	

Abbreviations: *APACHE II* Acute Physiology and Chronic Health Evaluation, *CPOT* Critical Care Pain Observation Tool, *DBP* Diastolic blood pressure, *HFOT* High-flow oxygen therapy, *hr* Heart rate, *ICU* Intensive care unit, *LUS* Lung ultrasound, *NIV* Noninvasive ventilation, *NRS* Numeric rating scale, *SBP* Systolic blood pressure, *RR* Respiratory rate, *SpO2* Peripheral oxygen saturations, *QoL* Quality of life

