### Randomisation and allocation concealment

Using the online randomisation system ‘Sealed Envelope™’ (that conceals allocation), an ICU research team member will randomise a patient once informed consent/informed advice has been obtained and demographic data collected. Participants will be randomised using a 1:1 allocation to either (A)-control arm (standard care) or (B)-intervention arm (MI-E plus standard care). Blinding of participants, clinicians, and outcome assessors will not be possible due to the nature of the intervention.

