#### Study arms

##### A. Control arm (standard care)

Patients will receive standard care in relation to mechanical ventilation, ventilator weaning, rehabilitation, standard physiotherapy techniques such as positioning, manual techniques (percussion, expiratory vibrations, expiratory shakes), manual/ventilator hyperinflation, endotracheal suctioning, and nebulisation. The use of MI-E will not be permitted in the standard care control arm. Respiratory physiotherapy treatments will be individualised to patient need at the discretion of the treating physiotherapist and not protocolised. Decisions to extubate and re-intubate will be at the discretion of the attending physician with reason(s) documented.

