#### Outcomes

Feasibility outcomes are listed in Table 2. Clinical endpoints will be collected to understand the feasibility of their collection informing conduct of a future adequately powered trial and not to conduct hypothesis testing related to causation. Feasibility will be assessed using pre-defined progression criteria (Table 3).

**Table 2 Tab2:** Feasibility outcomes

Feasibility outcome	Measurement detail
Proportion of eligible patients approached, consented, and randomised	Screening log and randomisation records
Proportion of MI-E treatment sessions completed	Case report form
Proportion of recruited patients with all clinical outcomes recorded	Case report form
Frequency of adverse events	Case report form
Attrition (participant withdrawal and loss to follow-up)	Case report form and withdrawal records
Acceptability of intervention and trial processes to participants and clinicians	Qualitative interviews Acceptability of intervention measure (AIM)/intervention appropriateness measure (IAM)/feasibility of intervention measure (FIM)
Acceptability of outcome measures to participants and clinicians	Qualitative interviews

**Table 3 Tab3:** Progression criteria (based on feasibility parameters)

	**Summary**	**Action required**
Go (green)	**Recruitment**: > 70% expected recruitment target **Follow-up**: > 75% data completeness **Adherence**: > 75% adherence to intervention	Feasible to continue to main trial
Amend (amber)	**Recruitment:** 50–70% of expected recruitment target **Follow-up**: 65–75% data completeness **Adherence**: 65–75% adherence to intervention	Identify remediable factors; discuss with trial management group
Stop (red)	**Recruitment**: < 50% of expected recruitment target **Follow-up**: < 65% data completeness **Adherence**: < 65% adherence to intervention	Do not progress to main trial, unless there is a strong case that unanticipated remediable factors have been identified

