#### Data management

All participants will be assigned a unique study identification number, which will be used in all study-related documentation. A record of names, contact details, hospital numbers, and assigned trial numbers will be stored securely using a password-protected Research Electronic Data Capture (REDCap) database only accessible to members of the research team.

Clinical study data will be inputted directly into REDCap by the treating clinician and subsequently validated by a member of the research team. Study participants completing an online EQ-5D-5L survey will enter data directly through an external user REDCap interface. Data recorded on paper will be entered into the REDCap database (by [name]).

Password-protected audio digital recording of interviews will be uploaded to a university computer secure drive. All transcriptions will be labelled with a unique study identification number, edited to ensure respondents are pseudonymised (only clinician profession and banding/grading documented), and stored securely adhering to university data protection policies.

Consent forms (and any other documentation) with personal identifiable data will be stored in a locked filing cabinet (or locked equivalent). Participant details will be anonymised in any publications that result from the trial. At the end of the study, pseudonymised data will be stored in a secure research data storage repository, alongside the other study data (as per sponsor policies).

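### Haemodynamic events, and at least one form of desaturation, count only if an undefined need for intervention is met, so their frequency mixes physiological change with unblinded staff response

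*Protocol article*

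**What the plan says.** Safety reporting introduces a list of session events with "We will record occurrence of the following during a MI-E treatment and control arm interventions". The list includes "HR, SBP, and DBP increase/decrease > 20% baseline and requiring intervention" and "acute desaturation to < 85% or > 10% below baseline and requiring intervention". Arrhythmia is also limited to cases needing intervention. Pneumothorax, accidental extubation and cardiopulmonary arrest carry no such limit. The section does not say when an intervention counts as required, or who decides.

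On knowledge of the allocated arm, Randomisation and allocation concealment states: "Blinding of participants, clinicians, and outcome assessors will not be possible due to the nature of the intervention". Data management adds: "Clinical study data will be inputted directly into REDCap by the treating clinician", with later validation by the research team. For control sessions, the Control arm section states: "Respiratory physiotherapy treatments will be individualised to patient need at the discretion of the treating physiotherapist and not protocolised".

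"Frequency of adverse events" is a feasibility outcome in Table 2. It is not among the progression criteria in Table 3, which cover recruitment, follow-up and adherence.

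Heart rate, blood pressure and oxygen saturation are clinical outcomes in both arms. Data collection schedules the clinical outcomes at three times: before the session, at its end and five minutes later. Table 1 marks these vital signs at only two: before the session and five minutes after it.

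**The concern.** Each haemodynamic event joins an objective limit to an action. Two patients with the same fall in blood pressure are counted differently if one is watched and the other is treated. The condition for treating is not defined, and the people around the bed know the arm.

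This matters because the Background says that adverse events from the exsufflation breath have not been studied. It also describes the adverse effects seen so far with MI-E in intubated patients as rare and short-lived. Short-lived changes are the ones that a filter on intervention is most likely to remove. The Background further reports that staff cite a lack of skill and knowledge as a barrier to MI-E, so a different readiness to act with this device is plausible. The findings are meant to inform a larger trial, and the event definition could be carried into it.

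**Working it through.** **Plan's own figure.** The article gives no expected adverse-event rate, so there is nothing to reproduce on this point. Its one precision figure concerns recruitment: 2 × 1.96 × √(0.25 × 0.75 / 200) = 0.120, which agrees with the stated 0.12 (95% level assumed). It has no bearing here.

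**What the definitions count**

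| Event | Objective limit | Intervention condition |
|---|---|---|
| HR, SBP, DBP change | > 20% from baseline | Yes |
| Desaturation, relative limb | > 10% below baseline | Yes |
| Desaturation, absolute limb | < 85% | Unclear from the wording |
| Arrhythmia | None stated | Yes |
| Pneumothorax, accidental extubation, cardiopulmonary arrest | Event itself | No |

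**Mechanism.** Let q be the proportion of sessions in which a limit is crossed, and r the probability that staff intervene given a crossing. Then:

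- recorded rate = q × r
- share of crossings not counted = 1 − r
- with the same q in both arms, recorded ratio (MI-E to control) = r(MI-E) / r(control), whatever q is

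**Illustration.** All values of q and r are assumptions. With q = 20% in both arms:

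| r, MI-E | r, control | Recorded, MI-E | Recorded, control | Ratio | Not counted, MI-E / control |
|---|---|---|---|---|---|
| 0.5 | 0.5 | 10% | 10% | 1.0 | 50% / 50% |
| 0.6 | 0.4 | 12% | 8% | 1.5 | 40% / 60% |
| 0.8 | 0.4 | 16% | 8% | 2.0 | 20% / 60% |
| 0.7 | 0.3 | 14% | 6% | 2.3 | 30% / 70% |
| 0.3 | 0.6 | 6% | 12% | 0.5 | 70% / 40% |

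For example, 0.20 × 0.6 = 0.12 and 0.20 × 0.4 = 0.08, a ratio of 1.5. Changing q moves the rates but not the ratio: for r of 0.6 and 0.4, q = 10% gives 6% and 4%, and q = 30% gives 18% and 12%. The distortion can run either way, and it vanishes when the two arms have the same r. The loss of crossings that prompt no action occurs in both arms whenever r is below 1.

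**Can the scheduled readings fill the gap?** Only in part. The events are those that occur during a session. The readings fall before it, after it and, according to Data collection but not Table 1, on its completion. No peak or lowest value within the session is scheduled. A brief in-session change that has resolved by the next reading would be seen in neither the event count nor the vital-sign data.

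**The case against.** The case for leaving the text alone has several sound parts.

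- **Little depends on the count.** The study is descriptive, no between-arm test is planned, and adverse-event frequency is not a progression criterion. This stands and limits the weight of the point.
- **Limiting the list to events that prompt action is a reasonable filter.** It keeps trivial fluctuations out. This stands as a reason to keep the current count, but not as a reason to report it alone.
- **Other text may capture milder changes.** Cardiovascular changes appear among the expected events without an intervention condition, the attending consultant assesses all adverse events, and reporting follows the sponsor's procedure. However, none of this text says that a crossing without intervention is counted, so it does not settle the matter.
- **Persisting changes remain visible** in the post-session vital signs. This is true for changes that last, not for those confined to the session.

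A reader might also infer more than the documents support:

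- *That the arms are in fact biased.* This needs different response probabilities by arm, and nothing in the article shows them.
- *That the objective readings needed are already collected.* They are not taken within the session.
- *That a saturation below 85% which staff merely observe is never recorded.* The condition may attach only to the second limb, in which case the absolute limb counts alone.
- *That the treating physiotherapist decides what requires intervention.* The article does not say. The treating clinician enters the data, the consultant assesses events and the research team validates. The article does say that neither clinicians nor outcome assessors are blinded.

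**Conclusion.** The point holds as a weakness of definition. For HR, SBP and DBP changes, and for at least the relative desaturation limb, the listed event requires an intervention that is nowhere defined and is decided without blinding. The resulting frequency is a product of physiology and response. It omits crossings that prompt no action, and it could differ between arms with no difference in physiology.

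Its size cannot be estimated from the documents. In the scenarios above the recorded ratio ranges from 0.5 to 2.3, with 20% to 70% of crossings uncounted, all under assumed values. Two wording problems can be read directly from the text: the unclear reach of the condition in the desaturation definition, and the different reading times in Data collection and Table 1. The change is worth making because it is cheap and gives a safety frequency that depends less on staff response. It does not threaten the feasibility conclusions.

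**What to change.** Keep the existing thresholds as they are, and make these changes:

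1. On the session form, in both arms, use two separate fields: (a) threshold crossed during the session, ticked from bedside monitoring and not derived only from the scheduled readings; (b) whether an intervention was given, and which.
2. Report by arm, per session and per patient, all crossings regardless of intervention, next to the present subset that required intervention.
3. Tabulate in addition the crossings seen at the scheduled post-session readings.
4. State whether the intervention condition applies to both desaturation limbs or only to the second.
5. Reconcile the reading times in Data collection with those in Table 1.

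The cost is one extra field per session and one extra table row, plus the attention needed to note crossings during the session. Staff must already notice a crossing to apply the current definition, so the added burden is small. More events will be listed, many of them minor.

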### Semi-structured qualitative interviews

Interviews with healthcare professionals and patients will explore the acceptability of the intervention and enrolment to the study. These interviews aim the following:Explore acceptability of the intervention for clinicians, patients, and consultees.Investigate potential barriers and facilitators to conducting a full trial.Determine outcome measures for a definitive trial.

#### Study design and recruitment

Interviews with patient participants in the intervention arm and their family members will take place within 6 weeks of discharge from ICU. We will exclude participants who have no recall of their ICU stay or the MI-E intervention. Interviews will be conducted by the chief investigator ([name]).

Clinician interviews will be conducted with staff from the ICU clinical team including doctors, nurses, and physiotherapists who have had exposure to the MI-E intervention within the preceding 4 weeks. These interviews will be completed by a member of the study team (SV) to eliminate potential bias presented due to a working relationship with ES. These will occur during trial recruitment and within 4 weeks of exposure to a patient in the intervention arm of the trial.

We have based the interview topic guides on the Theoretical Framework of Acceptability (TFA) [25]. Interviews will be completed virtually via an online platform (Microsoft Teams).

#### Sampling and recruitment

Convenience sampling of 10–15 participants [26] will be used. Clinicians will be approached based on gaining maximal variation sample regarding profession and years of clinical experience. Patients and family members recruited into the study will be approached for consent once the patient has been discharged from ICU.

#### Interview data collection and analysis

On interview commencement, we will collect clinician demographic data (clinical profession, years working in profession and on ICU, highest educational level obtained) and patient demographics including age, reason for ICU admission, ICU LOS, or family demographics (relationship to patient) as relevant to the interview participant.

Interviews will be digitally recorded and transcribed verbatim by a university-approved transcription service. Transcripts will be checked for accuracy and anonymised. Data will be analysed using reflexive thematic analysis [26, 27] and using TFA domains through first-level coding by ES. Thematically similar responses will be grouped in a process of data reduction and compared across transcripts. Tables will be produced to highlight key thematic content, within each TFA domain with consideration of responses from both patients and clinicians and with the aim of highlighting similar and discordant themes. Domains will be identified as salient based on their frequency of inclusion and potential strength of impact. NVivo software will be used to support this process.

